**III.b. Population**

Patients with attention deficit hyperactivity disorder will be recruited by letter and email to the Psychiatric Association of Bahia (APB), Bahia Neurology Society (SNB) and the Brazilian Association of Neurology, Psychiatry and Allied Professions (ABENEPI) - chapter Bahia. We will also contact by mail and telephone, professional experts in ADHD, inviting them to refer potential patients for the study. We will also publish advertisements on the internet and on social networks, from October 2012 to December 2012, according to the inclusion criteria.

III.b.1. Inclusion criteria

-Ability to understand and sign the informed consent form;

-Diagnosis of attention deficit-hyperactivity disorder according to DSM-IV-TR and Adult Self-Report Scale (ASRS);

-Residents in Bahia;

-18 years old or older;

III.b.2. Exclusion criteria

-Major psychiatric disorders such as schizophrenia and bipolar disorder;

-Inability to understand the questionnaires applied (cognitive impairment- score ≤ 24 on the Mini-Mental State Examination) or illiterate;

-Abuse of psychoactive substances or alcohol, except nicotine and caffeine, during the last 12 months.

III.b.3. Sample size

This will be a randomized sample of ADHD individuals recruited through Internet media, social networks, and contact with ADHD experts and specialized societies of neurology, psychiatry and related fields, during the study period. A sample size of 50 subjects was calculated assuming a difference in proportion between the active tDCS and sham control groups of 40% on the Go/ No go performance, before and after interventions.

This calculation was performed using the statistical program STATA 12.0, considering an alpha of 0.05 and a power of 0.80, resulting in an sample of 25 subjects in each group, intervention and control. To address unexpected factors, we applied a drop-out rate of 20%, reaching a total sample size of 60 individuals.

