**III.c. Study Variables**

III.c.1. Dependent variables

The following variables will be evaluated: neuropsychological outcome (Go/ No tasks); power analysis of frequency bands through QEEG; and brain reconstruction network model of each individual by QEEG.

III.c.2. Independent variables

Transcranial direct current stimulation and sham procedure.

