**III.d. Procedures**

After screening through psychiatric interview, explanation about all steps of this study, and agreement expressed through signed informed consent form, ADHD patients will underwent a cognitive evaluation through the Mini-mental state examination (MMSE), Mini International Neuropsychiatric Interview Brazilian (MINI PLUS), Adult Self-Report Scale (ASRS), Quality Questionnaire life in Adults with ADHD (AAQoL), and an interview through a questionnaire. This evaluation script is an instrument based on the ADHD diagnostic criteria from DSM-IV-TR, and consists on epidemiological and clinical questions.

Individuals will be divided into two groups by block randomization, aiming at a balanced distribution between the groups (30 subjects each). Blocks shall be composed of 10 subjects, totaling six blocks. To compose each group will be called 5 individuals from each block.

Following it, the brain electrical activity will be recorded by EEG with 32 channels placed on the scalp acoording to the 10-20 EEG international system, during 5 minutes. The recording will be in a resting state, the first minute with eyes open looking for a fixed point, and the last 4 minutes with eyes closed. Then, participants will be asked to perform tasks on the computer: two Go / No go tasks adapted from the original version, the first using as a target a fruit and the second a letter. After the cognitive tasks, subjects will undergo active or sham stimulation, according to the previous randomization.

Participants of the intervention group will be submitted to tDCS at 1mA, anodal electrode over the left dorsolateral prefrontal cortex and cathodal electrode over the equivalent area on the right side. On control group subjects (sham group), electrodes will be placed at identical positions and sham stimulation will be applied. The stimulation device will turn on for only 30 seconds so that the patient will feel the initial sensation, then shutting down. The intervention and sham procedure will take place in one single session of 20 minutes to evaluate the immediate effect.

At the end of the intervention, subjects will perform again two Go/ No go tasks (randomly selected to avoid learning effect), and they will undergo another EEG recording, with the same previous technical caracteristics.

This study will be performed at Laboratory of Functional Electrostimulation at Federal University of Bahia.

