**III.e. Statistical Analysis**

**Step 1**: socio-demographic, clinical and epidemiological description of the groups, using the usual procedures of descriptive statistics such as calculation of frequencies, measures of central tendency and dispersion;

**Step 2**: characteristics will be compared between groups at the baseline, using one-way analysis of variance (ANOVA) for continuous variables and chi-square test for categorical variables;

**Step 3**: Shapiro-Wilk test will be performed to assess normality assumption of the outcome variables;

**Step 4**: analysis of paired and independent samples using the t-test for comparison within each group and between intervention groups, or applying equivalent non-parametrics tests (according to Shapiro-Wilk test results), before and after intervention;

**Step 5**: Person's chi-square to evaluate blinding effectiveness, comparing between groups.

These analysis will be performed through Stata, version 12.0 for Windows. Results will be considered statistically significant if p ≤ 0.05.

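### No primary outcome or deciding Go/No-go score is named and every result is judged at p ≤ 0.05, so the trial's false-positive rate is not held at the 0.05 used for sizing

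*Protocol*

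**What the plan says.** Protocol III.c.1 lists three dependent-variable domains and calls none of them primary: "neuropsychological outcome (Go/ No tasks); power analysis of frequency bands through QEEG; and brain reconstruction network model of each individual by QEEG". The behavioural domain is itself two tests. Section III.d describes "two Go / No go tasks adapted from the original version, the first using as a target a fruit and the second a letter", repeated after stimulation, and names no score for either.

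Section III.e, Step 4, compares outcomes both within each arm (before against after) and between arms, by t-test or a non-parametric equivalent. One decision rule closes the section: "Results will be considered statistically significant if p ≤ 0.05". No hierarchy among the tests is given.

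The sample size in III.b.3 rests on a "difference in proportion between the active tDCS and sham control groups of 40% on the Go/ No go performance", "considering an alpha of 0.05 and a power of 0.80". Objective I.b.1 is the only specific objective worded as tDCS against sham, and it names Go/No-go. Section II, however, says that efficacy on inhibitory control will be shown by behavioural and neurophysiological parameters together.

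**The concern.** An alpha of 0.05 describes the error rate of one identified test. The protocol sizes the trial for such a test but does not say which analysed result it is. A favourable p-value could come from either task, from any score on it, from a before-after change in the active arm alone, or from an EEG or network measure. Each would meet the stated rule, and section II allows the neurophysiological results to count towards the efficacy claim.

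The within-arm tests deserve separate mention. The protocol itself guards against a learning effect on the repeated tasks (III.d). If practice remains, the active arm can improve significantly with no effect of stimulation, and the rule in III.e would still call that result significant.

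At stake is the meaning of the trial's main conclusion. A reader could not tell whether a positive report rests on the comparison the trial was sized for or on one of several others.

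**Working it through.** **Inputs from the protocol.** Threshold p ≤ 0.05 (III.e). Alpha 0.05, power 0.80, a 40-point difference and 25 per arm (III.b.3). Three outcome domains (III.c.1). Two Go/No-go tasks (III.d). Within-arm and between-arm tests (III.e, Step 4). **Assumed, because not given:** two-sided testing, the base proportions, the number of tests, and the correlation between them.

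**Step 1. The plan's own figure.** With pooled variance, n per arm = [1.96·√(2p̄(1−p̄)) + 0.8416·√(p₁(1−p₁) + p₂(1−p₂))]² / (p₂−p₁)².

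- 0.3 v 0.7: (1.386 + 0.545)² / 0.16 = 23.3, so 24 per arm.
- 0.5 v 0.9: (1.270 + 0.491)² / 0.16 = 19.4, so 20 per arm, or 25 with a continuity correction.

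The stated 25 per arm is therefore reproducible as a single two-sided between-arm comparison of two proportions at 0.05. That is the test to which the alpha and power belong.

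**Step 2. Can that test be found in the analysis section?** Not clearly. Step 4 of III.e analyses outcomes by t-test or a non-parametric equivalent. Chi-square appears only for baseline categories (Step 2) and blinding (Step 5). Neither the proportion used for sizing nor the task it comes from is identified among the analysed outcomes.

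**Step 3. How many tests does the text allow?** The count is not stated. The least is one between-arm test per domain, which is 3. Adding the paired test in each arm gives up to 3 tests per measure, so 3 × 3 = 9 even with one measure per domain. If each of the two tasks yielded three scores (assumed: commission errors, omission errors, reaction time), the between-arm Go/No-go tests alone would number 2 × 3 = 6.

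**Step 4. Chance of at least one p ≤ 0.05 when nothing differs.** For k independent tests this is 1 − 0.95^k. The correlated figures come from simulating k equally correlated normal test statistics, 20,000 runs each.

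| Tests k | 0.95^k | Independent | Correlation 0.5 | Correlation 0.7 |
|---|---|---|---|---|
| 3 | 0.857 | 14.3% | about 12% | about 11% |
| 6 | 0.735 | 26.5% | not run | not run |
| 10 | 0.599 | 40.1% | about 28% | about 21% |

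These figures assume no true change of any kind. They do not include the further risk that practice makes a within-arm test significant.

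**Step 5. Cost of the alternative.** If the three domains were kept co-equal and Bonferroni-adjusted (0.05/3 = 0.0167), power at 25 per arm would fall from 83% to 68% for 0.3 v 0.7, and from about 90% to 78% for 0.5 v 0.9. A single named primary outcome keeps alpha at 0.05 and, if it is the proportion used for sizing, keeps 25 per arm.

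**The case against.** The strongest reply is that Go/No-go is already the main outcome in substance. It is listed first, it is the only outcome the sample size uses, and it is the only one tied to a comparison with sham in the specific objectives. The QEEG and network objectives (I.b.2, I.b.3) are worded descriptively. This stands, and it would be wrong to say that the protocol treats the three domains as equals. It does not settle which task, which score or which contrast decides, and section II still brings the neurophysiological measures into the efficacy claim.

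A second reply is that multiplicity methods belong in an SAP, which may exist. For the handling of EEG bands, channels and network indices this is fair, and their absence here is no fault. Naming the result that decides the trial is different: it is protocol content, and this protocol itself fixes the significance rule.

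A reader might go further and infer that a chance positive is nearly certain, by multiplying "the brain electrical activity will be recorded by EEG with 32 channels placed on the scalp" by, say, five frequency bands. That gives 160 tests, 160 × 0.05 = 8 expected false positives, and 1 − 0.95^160 above 99.9%. The documents do not support this. The 32 channels describe the recording, no number of bands is given, and electrode-by-electrode testing is not stated. Measures from one recording are also correlated. With independent tests it takes 45 to reach 90% and 59 to reach 95%, and nothing in the protocol commits to that many.

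**Conclusion.** The point holds in this form. Go/No-go has implied priority, but no primary outcome, deciding task or deciding score is named, and one unadjusted threshold covers between-arm, within-arm, behavioural and EEG-derived results alike. The error rate of the efficacy claim is therefore not held at the 0.05 used for sizing.

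With one between-arm test per domain, the chance of at least one false positive is about 12% to 14%, more than twice the nominal rate. With ten tests it is about 28% to 40%. The lower figures assume a correlation of 0.5 and the upper ones independence. Stronger correlation lowers them and more tests raise them. Because the protocol gives no count, these sizes are illustrations and not estimates. The defect is the missing decision rule, and it does not depend on any one of these figures.

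**What to change.** In III.c and III.e, name one between-arm Go/No-go measure as the single primary outcome, tested at two-sided 0.05, and state that the efficacy conclusion rests on it alone. One suitable example is the commission-error rate on No-go trials, combined over the fruit and letter tasks and compared between arms after stimulation with adjustment for baseline. The choice of score is the investigators' to make, since the documents do not fix it.

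The chosen measure must match III.b.3. A proportion of participants and a mean error rate per participant are different quantities, and the protocol gives no standard deviation for the latter. Either define the primary outcome as the proportion that was used for sizing, or restate the sample-size justification for the measure chosen.

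Label the other Go/No-go scores and all within-arm tests secondary. Label the QEEG and network measures exploratory, with no efficacy claim from their unadjusted p-values, and amend section II to agree. Detailed multiplicity methods for the EEG families can be left to the SAP.

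The cost is protocol wording, settled before data are seen, and possibly a reworded sample-size justification. The real downside is that an isolated secondary, within-arm or EEG p-value can no longer be presented as proof of efficacy.

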**III.f. Study limitations and strategies to avoid bias**

III.f.1. **Selection bias**: it will be used objective criteria and already widely applied for the diagnosis of attention deficit-hyperactivity disorder, then it is unlikely the possibility of inclusion of individuals with other diagnosis.

III.f.2. **Measurement bias**: the selected scales are instruments with recognized and acceptable validity and reliability.

**IV. ETHICAL ASPECTS**

The present study strictly follows the ethical principles in research involving human subjects, according to the Declaration of Helsinki. All participants will be informed about the nature of the study and the all procedures. It will be included only those that sign informed consent form, in accordance with Resolution 196/96 of the National Health Council (Brazil) [23]. The signature of a witness will be required considering those patients unable to sign the free and informed consent form.

**V. TECHNICAL, SCIENTIFIC AND FINANCIAL FEASIBILITY**

The purpose of this study is to assess neurobiological aspects associated with attention deficit-hyperactivity disorder and the contribution of transcranial direct current stimulation to modulate inhibitory control and neurophysiological parameters, demonstrated by neurocognitive tasks (Go/ No go), QEEG and brain reconstruction network model. This study will not interfere with usual treatment of ADHD individuals, to avoid bringing any harm to those due treatment interruption. Through the investigation of the effectiveness of a simple technique, applied over the prefrontal cortex, it is expected to increase the inhibitory control in ADHD individuals. We also expect that the present trial will contribute scientifically to the development of neurophysiological assessment methods, for the study of ADHD, and to the evaluation of the applicability of a low cost, non-invasive and safe technique for otimization of inhibitory response in this population.

The project's budget has been reviewed and approved by [name]. [name], and include costs of materials used in the data collection. The laboratory where the data collection will be held, already has the equipment needed as tDCS devices, 32 channels EEG, computers, besides electrodes, cables and sponges, being estimated only a very low expense with materials such as questionnaires, which explains the low budget and reiterates its financial feasibility.

**VI. RELEVANCE**

The results of this clinical trial will allow us to evaluate behavioral and neurobiological aspects of the attention deficit-hyperactivity disorder, besides to observe socio-demographical and clinical-epidemiological parameters in this population.

It will also be assessed, as mentioned previously, a low cost, simple and non-invasive technique for the modulation of the inhibitory control.

To the best of our knowledge, this trial will be the first study to assess the cognitive and neurophysiological effects of tDCS on ADHD patients. In the long term, we expect that our results might reinforce comprehensive programs of intervention and multidisciplinary approach in patients with ADHD.

**VII. SCHEDULE**

After the project approval, by this Institutional Review Board, the recruitment will start on May 2013, with data collection from June 2013. It is expected that the initial data analysis occurs approximately on March 2014, followed by elaboration of the thesis and scientific papers, during the second semester of 2014.

